**11.2. Methods and data analysis models**

The impact of the intervention will be analyzed using the "difference in differences" method: the difference in the prevalence of anemia for children 2 to 5 years or the difference of average hemoglobin levels, i) between the treatment and the control group and ii) between the beginning and the end of the intervention. It will be possible to use a propensity score, determined from the baseline characteristics, in order to check the comparability between groups and, if necessary, to use the score as an adjustment factor. All tests performed will be unilateral, with a 95% confidence interval. The analysis will be performed using STATA 12.0 (Stata statistical software, Stata Corporation, College Station, Texas USA).

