# 5. Study design

The study will be randomized and single-blind. Of the 4 collection routes (Figure 1), 500 milk containers are collected every day, corresponding to an average of 2 households of herders per container. Randomization will be made at the level of household concessions, with certain concessions receiving fortified Thiakry and others making up the control group.

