# 7. Number of subjects

Calculating the number of required subjects is based on the main assessment criterion of the nutrition component of the study: anemia. Considering that the consumption of fortified Thiakry by children has the potential to reduce the prevalence of anemia by 15%, from an average prevalence of 75% to 60%, the number of required subjects is 165 subjects per group, totally 330 subjects, with 80% power and 5% alpha (unilateral test). This is a cluster trial, with the the concession as the randomization unit. We have therefore taken into account an intracluster correlation coefficient of 0.3, which gives an estimate of 430 children aged 2-5 years required. Estimating an attrition of 20%, we would need to recruit 550 children. Moreover, it is likely that not all households will participate in the study (largely due to the phenomenon of transhumance in the area) and that not all households will achieve their objective in terms of milk production in order to obtain the incentive. Among children in the group receiving the fortified Thiakry, there is no guarantee that all of the product will be consumed and at the necessary frequency (every day) to see a reduction of anemia. We therefore estimate that another 20% of the number of households may ineligible for analysis, bringing the total number of subjects required to 660 children. As the number of households of the area is approximately 700, with an average of 2 children in the age group of interest per household, we are confident that we will be able to access the necessary number of children.

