**10.3. First household data collection (Baseline)**

An initial survey of households will take place in January 2013 to gather baseline data. The questionnaire, in Fulani, will collect data related to:
- Composition of the household
- Herding/cows (size of herd, etc.)
- Crops (crop type, etc.)
- Socioeconomic status (household goods, level of education, etc.)
- Household food consumption (frequency, food security, etc.)

Additionally, measurements of hemoglobin levels will be conducted for children 6 months to 5 years, as well as their mothers, by drawing a drop of blood using a lancet and placing it in a microcuvette, allowing a direct reading of the result using a HemoCue® Analyzer

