# 11. Biometrics and data analysis

**11.1. Results analysis plan**

A descriptive analysis will first be carried out, along with a comparison of baseline characteristics between both groups: proportion of children who are anemic, average hemoglobin levels, attrition of households etc. Covariates collected during the study at baseline (socio-economic level of the household, household composition etc.) corresponding to the two groups will be compared through univariate analysis. The efficacy of treatment will be evaluated using an adjusted multivariate analysis, adjusting using covariates that may have a confounding factor: length of participation in the study or covariates whose distribution is different between the 2 groups.

The analyses will be performed on the main response variable "proportions of households respecting the contract outlined at the beginning of the study", in terms of volume and milk collection frequency. These proportions will be compared between the two groups.

Secondary responses variables (proportion of children presenting mild, moderate or severe anemia; proportions of children with stunting, undernutrition or wasting) will be analyzed on the intent-to-treat population, gathering all the children who were attributed to a group for whom hemoglobin measurement results are available over 6 months, regardless of the group. The analysis will be adjusted for age and risk factors for anemia if their distributions are different between the two groups.

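### Section 7 sizes one follow-up comparison of anemia but Section 11.2 plans a difference in differences; with no baseline/follow-up correlation given, the power of the planned analysis is undocumented, and adjusting for baseline would be more precise

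*Protocol*

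**What the plan says.** Protocol Section 5: "The study will be randomized and single-blind". Concessions are the unit of randomisation, and Section 8 describes the draw as a lottery. The Summary says that the same children are visited at baseline, 6 months and 1 year. Section 10.3 (Baseline) provides the starting value: "measurements of hemoglobin levels will be conducted for children 6 months to 5 years".

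Section 7 bases the calculation on the belief that fortified Thiakry "has the potential to reduce the prevalence of anemia by 15%, from an average prevalence of 75% to 60" per cent. It concludes that "the number of required subjects is 165 subjects per group, totally 330 subjects, with 80% power and 5% alpha (unilateral test"). It then allows for clustering ("We have therefore taken into account an intracluster correlation coefficient of 0.3") and arrives at 430 children. Neither a baseline measurement nor a correlation over time enters this calculation.

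Section 11.2: "The impact of the intervention will be analyzed using the 'difference in differences' method". It applies this to anemia prevalence or mean hemoglobin, between groups and between the start and end of the intervention, with one-sided tests and an optional propensity score.

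Section 11.1: "The efficacy of treatment will be evaluated using an adjusted multivariate analysis". The covariates are length of participation and whatever differs between the groups. The baseline outcome is not named as one of them.

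**The concern.** The sizing and the analysis use different estimators. A comparison of follow-up prevalences has a variance that is fixed by the two prevalences. A difference in differences adds the baseline variance and subtracts a term in rho, so it can be less or more precise than the comparison that was sized. The 80% in Section 7 therefore does not describe the analysis in Section 11.2.

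The choice of method also has a cost. With allocation by lottery, expected baselines are equal, so subtracting baseline is not needed to remove bias. Regressing follow-up on arm and baseline estimates the same effect and lets the data set the weight given to baseline, whereas subtraction fixes that weight at one. Subtraction also over-corrects a chance imbalance by about (1 − rho) times its size. Anemia is the outcome on which the trial is sized, so the loss falls where precision was planned for.

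**Working it through.** **Inputs from the protocol.** Prevalences 0.75 and 0.60, 165 per group, one-sided 5%, ICC 0.3, 430 children after clustering, and on average 2 eligible children per household (Section 7). **Assumed:** baseline prevalence 0.75 in both arms; the same rho in both arms, over a range; two children per concession (the protocol gives the figure per household); and 165 as the effective size after clustering.

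**The plan's own figure.** With mean prevalence 0.675, the standard two-proportion formula is n = [z_α√(2·0.675·0.325) + 0.842√(0.1875 + 0.24)]² / 0.15².
- Two-sided 5%: 151.9, so 152. With the continuity correction n/4·[1 + √(1 + 4/(0.15n))]² it is 164.9, so 165, which matches.
- One-sided 5%, as labelled: 120, or 133 with the correction.
- Clustering: 330 × (1 + (2 − 1) × 0.3) = 429, stated as 430.

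So 165 is a comparison of two independent proportions at a single time. It is larger than the stated one-sided test needs, and that slack matters below.

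**Variances (per child per arm, both arms summed).**
- Follow-up only: 0.75·0.25 + 0.60·0.40 = 0.1875 + 0.24 = 0.4275.
- Difference in differences: 3·0.1875 + 0.24 − 2·rho·[0.1875 + √(0.1875·0.24)] = 0.8025 − 0.7993·rho.
- Follow-up adjusted for baseline (large-sample): 0.4275·(1 − rho²).

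**Power** = Φ(0.15/√(V/165) − 1.645). Example at rho 0.3, difference in differences: V = 0.5627, SE = 0.0584, 0.15/SE = 2.569, Φ(0.924) = 82%. Follow-up only gives 90% at any rho.

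| rho | Difference in differences | Baseline-adjusted | Variance ratio |
|---|---|---|---|
| 0 | 69% | 90% | 1.88 |
| 0.1 | 73% | 91% | 1.71 |
| 0.2 | 78% | 91% | 1.57 |
| 0.3 | 82% | 93% | 1.45 |
| 0.4 | 87% | 94% | 1.34 |
| 0.5 | 92% | 96% | 1.26 |
| 0.6 | 96% | 98% | 1.18 |

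**Break-even points.**
- 80% power needs V = 165·0.0225/(1.645 + 0.842)² = 0.600, so rho = (0.8025 − 0.600)/0.7993 ≈ 0.25.
- Equality with follow-up only: rho = (0.8025 − 0.4275)/0.7993 ≈ 0.47.

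**Stable concession effects.** The table applies the cross-sectional design effect to the change score, although stable concession effects cancel in a change. Take 215 actual children per arm (430/2), ICC 0.3 and fully stable concession effects. At rho 0.3 the difference in differences has V = 0.5627 + 0.3·(0.8025 − 0.7993) = 0.5637, and power Φ(0.15/√(0.5637/215) − 1.645) = 90%. At rho 0.4 it is 94%. If only half of the concession correlation persists, the figures are 84% and 88%. Follow-up only has V = 1.3·0.4275 = 0.5558 and 90%. Baseline adjustment at rho 0.3 with full stability gives about 95%, so its advantage remains.

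**The case against.** The strongest defence concerns how households enrol. The lottery is drawn at the first information meeting (Sections 8 and 10.1). The signed intent form comes back 10 days later, and consent is taken when enumerators visit. Households therefore join knowing their arm, and the control arm gets no incentive during the study. If this creates a baseline difference that is stable over time, the difference in differences removes all of it, while baseline adjustment removes only about a fraction rho. As an illustration, at rho 0.3 a stable 5-point difference would leave (1 − 0.3) × 5 = 3.5 points. This stands as a real downside of the change. It is a reason to keep the difference in differences in the plan, though not as the main analysis.

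The second defence is that low rho is unlikely. Section 7 assumes a correlation of 0.3 between different children of one concession, so the same child measured twice should correlate at least about that much if concession effects persist. That puts rho above the 0.25 break-even. The argument is reasonable, but persistence over six months is itself an assumption, and the protocol makes no such statement.

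Three stronger readings are tempting, and the protocol does not support them.
- *The planned analysis is underpowered.* Under the stated one-sided test with 165 per group, it exceeds 80% once rho passes about 0.25. Two-sided power would be lower (73% at rho 0.3), but a two-sided test is not what Sections 7 and 11.2 specify.
- *The baseline is wasted.* A difference in differences uses the baseline, only with a fixed rather than an estimated weight.
- *Sections 11.1 and 11.2 contradict each other.* They can be read together, because a difference-in-differences regression can carry covariates. What is missing is a statement that they describe one model.

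**Conclusion.** The point holds as one of efficiency and documentation. Section 7 sizes a follow-up comparison, Section 11.2 plans a different contrast, and no rho connects them. The power of the planned analysis is therefore unknown, at about 69% to 96% for rho 0 to 0.6, and somewhat higher with stable concession effects. A shortfall below 80% is not shown, and under randomisation the estimate is unbiased.

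The loss against baseline adjustment is present at every correlation tabulated; only its size depends on rho. Against a plain follow-up comparison, the difference in differences loses only below rho of about 0.47, on the same effective-size basis.

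These figures rest on equal expected baselines of 75%, a common rho, a normal approximation and two children per concession. They also rely on the slack in 165: at the 120 per group that the one-sided test needs, the difference in differences would have 57.5% power at rho 0 and 70.7% at rho 0.3. Power for mean hemoglobin was not computed, because the protocol gives no standard deviation.

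**What to change.** - **Section 11.2:** make the main nutrition analysis a regression of follow-up anemia (or hemoglobin) on arm and the child's own baseline value, with standard errors clustered on the concession. Report a risk difference for anemia.
- **Section 11.1:** state that this is the adjusted multivariate analysis meant there, and name the baseline outcome as a covariate whether or not it differs between groups.
- **Section 11.2:** keep the difference in differences as a pre-specified sensitivity analysis, giving as the reason that the lottery precedes consent and the baseline survey.
- **Section 7:** state that the calculation is for the follow-up comparison and takes no credit for baseline adjustment. If the difference in differences is kept as the main analysis instead, give rho with a justification and recompute the sample size.

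The cost is wording in three sections and no new measurements, because baseline hemoglobin is already collected. There are two downsides. Children without a baseline hemoglobin need a simple rule, such as mean imputation with a missingness indicator. And if arm-aware enrolment produces a stable baseline difference, the main analysis removes only part of it, so a clear disagreement with the sensitivity analysis should be reported and discussed.

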**11.3. Attrition**

Attrition will comprise households who have moved out of the area reached by collection routes and/or who have decided to go on transhumance and to leave the study voluntarily. The reasons for attrition will be recorded by enumerators. The characteristics of these households will be compared with those of households who participated all the way to the end of the study.

**11.4. Blinding**

As much as possible, the enumerators will not have knowledge of the intervention group at the time of the hemoglobin and anthropometric measures or at the time of questionnaire data collection.

# 12. Administrative procedures and considerations/Practical aspects

**12.1. Partners**

GRET will oversee the implementation of the study, recruitment of households, and random group assignment. An agreement between GRET, LDB, PPZS (Pastoralisme et Zones sèches en Afrique de l’Ouest), and IFPRI will be signed in order to share the data and human, financial, and logistical resources. This will ensure synergy in their actions, as they work together to promote the integration of the research results into future economic and social development initiatives and to share the results to meet the population’s evolving needs. Gaston Berger University will be responsible for the implementation of the data collection and CLM for the implementation of the awareness campaign.

**12. 2. Monitoring and data management**

The questionnaires will be entered directly on tablets (PDA) by enumerators recruited for data collection by Gaston Berger University (Saint-Louis). The data will then be processed anonymously (using unique identifiers).

**12.3. Ethical and regulatory aspects**

This study will be carried out in accordance with the research protocol; with the text of the Helsinki Declaration (adopted by the World Medical Assembly in June 1964 with amendments in Tokyo (1975), Venice (1983), Hong Kong (1989), Edinburgh (2000), Washington (2002), Tokyo (2004) and Seoul (2008)); and with the recommendations of good clinical practice (ICH, May 1996). It will also proceed in accordance with the laws and regulations of Senegal pertaining to matters of health research. This project was jointly submitted to the National Ethics Committee for Health Research in Senegal (CNERS) and the ethics committee of IFPRI.

**12.4. Information sharing, archiving, and document storage at the end of the study**

The partners have agreed not to share the raw data present in the databases. In particular:
- Trade secrets of LDB (preparation of recipes including Thiakry) cannot be shared. Only fortification levels and associated molecules may be detailed in research publications.
- Data collected daily by LDB will not be used for publications that will be made public within 6 months after the data’s collection.

- Data from household surveys conducted by IFPRI, GRET, and PPZS will not be disseminated in raw format without the agreement of the institution who collected them. In all cases, the last names, first names, geographical coordinates, and all other identifying information cannot be diffused to third parties.

- The source of all data should be clearly mentioned during oral communications (presentations) or written communications (publications).

The principal investigators and the coordinating center will archive and keep documents related to the study for a period of at least 30 years. These documents will include the protocol of the study and the informed consent of mothers, as well as any administrative documents.

**13. Publications**

The results of the research will be owned by IFPRI, which undertakes to disseminate them to LDB and the general public through technical fact sheets, articles in international journals, and communications during national and international meetings. Researchers involved in the project, regardless of nationality, will be cited in articles that come from the research. A final report will be delivered at the end of the study to different participating institutions, CLM, and the National Ethics Committee for Research in Health Senegal (CNERS).

**14. Financing**

Funding for the study comes from the European Union, through its CRP4 program "Agriculture for Nutrition and Health".

1. A "Value Chain" is a supply chain in which value is added to a product as it advances along the chain. It is described by the series of activities and actors involved along the value chain and how and when the value is added by these actors (Hawkes & Ruel, 2010). The supply chain includes all operations beginning with inputs such as raw materials and incorporating all the changes required to achieve the final product. It is based on a contractual relationship between the actors. [↑](#footnote-ref-1)
